#### Procedure for data collection for the focus Group Interviews

There will be sixteen focus group interviews with 8–10 participants including schoolteachers, school principals, school nurses, SEN students and their parents will be conducted to gain an in-depth understanding of the views and experiences after participated in the SWELE program and to explore the mental wellbeing of the SEN students participating in the SWELE program. Interview guide will be developed based on literature review as follows:

#### Interview guides:

Tell me the experiences in participating the SWELE program.What do you like the best of the SWELE program?What do you like the least of the SWELE program?Would you recommend the SWELE program to your friends and why?Anything you would like the SWELE program to be improved?

### Statistical analysis

Appropriate descriptive statistics, such as mean (standard deviation), median (inter-quartile range) and frequency (percentage) will be used to summarize and present the baseline characteristics and outcome data of the participants. Normality of continuous variables will be assessed based on their skewness and kurtosis statistics, values within ± 2 indicating the plausibility of normal distribution [19]. Suitable transformations will be made on skewed variables before subjecting them into inferential analysis. Paired sample t-test will be used to compare the change of each outcome (mood, anxiety, social, playfulness) at post-test with respect to pre-test within group and subgroups (age and gender). All statistical analyses will be performed using IBM SPSS 28 (IBM Crop., Armonk, NY) with level of significance set at 0.05.

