## Methods

SWELE program is a 16-week program combining unstructured outdoor play with mindfulness-based activities to promote mental wellbeing among SEN students, in the context of the COVID-19 pandemic. The protocol was prepared according to the SPIRIT checklist (Additional file 1).

This is a mixed methods study design. Study measurements will be conducted in the two-time points [baseline Pre-test and Post-intervention] for data collection using six questionnaires to evaluate the project objectives and impact in the following. Sixteen focus group interviews will also be conducted from six special schools after participated the SWELE program. The focus group interview may last 40–60 minutes.

There are six questionnaires in this study and their details are in the followings:

Demographic information sheet

The demographic sheet will include name, age, gender, grade and medical diagnosis. (see Appendix I)

2.Emoji Mood Scale

To be inclusive and accurately capture each SEN student’s self-report on mood and emotion, it is useful to present visual stimuli in association with text. The Emoji Mood Scale includes five different emoji with a 5-points response scale of mood ranging from 1–5: 1-Very bad; 2-bad, 3-so-so, 4-good; to 5-very good [11]. The range of scale score can be from 1 to 5 where higher scores represented very good mood and emotion. The mood scale with the Chinese descriptor for each emoji mood scale can be found in Appendix II.

3.Six-item Short-form of State-Trait Anxiety Inventory (STAI-6)

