### Population

Grade 1- Grade 12 SEN students (children and adolescents) will be enrolled from six selected special schools in Hong Kong. Inclusion criteria of study participants are: 1) students are studying in a special school; 2) students can speak and understand Cantonese; 3) students have no diagnosis of any cardiovascular disease; 4) parental consent obtained. Exclusion criteria of the study are: 1) students are not studying in the special schools; 2) students do not speak and understand Cantonese or English; 3) student has diagnosis of cardiovascular disease; 4) student cannot provide parental consent.

There will be 1,063 children and adolescents aged 6–18 years old with mild to moderate physical and intellectual disabilities (ID) from the six selected special schools will be recruited to participate the SWELE program implemented by the research team (Fig. 1). Based on our team’s experience, it is anticipated that at least 90% of them are eligible and willing to join the program, and the attrition rate would be less than 10%. It is therefore expected to have at least 850 children completing the program and outcome assessments. Such a sample size (*n* = 850) allows to detect a change in an outcome of effect size as small as 0.1 with 80% power at a level of significance of 0.05 (2-sided). An effect size of 0.1 is conventionally regarded as small [17].

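### The plan transforms skewed outcome variables before a paired t-test, although that test depends only on the within-student differences

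*Protocol article*

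**What the plan says.** The protocol article, under Statistical analysis, sets out a three-step rule.

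1. Screening: "Normality of continuous variables will be assessed based on their skewness and kurtosis statistics", with "values within ± 2 indicating the plausibility of normal distribution".
2. Remedy: "Suitable transformations will be made on skewed variables before subjecting them into inferential analysis".
3. Test: "Paired sample t-test will be used to compare the change of each outcome", post-test against pre-test, in the whole group and in age and gender subgroups.

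The outcomes are bounded scores. Under Methods, mood is a single item on "a 5-points response scale of mood ranging from 1–5", and the STAI-6 is given a score range of 6 to 24. Under Population, the study is "expected to have at least 850 children completing the program and outcome assessments", and that number "allows to detect a change in an outcome of effect size as small as 0.1 with 80% power", two-sided at 0.05.

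The object of the screening is described only as continuous variables. The post-minus-pre differences are not mentioned. The variables that enter a paired t-test are the pre and post scores, so the natural reading is that these are screened and, if skewed, transformed.

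**The concern.** A paired t-test is a one-sample t-test on the within-student differences. It assumes nothing about the shape of the pre or post scores taken separately. Screening those scores therefore examines a distribution that the test does not use.

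On a bounded scale, skewness of the scores is to be expected whenever most students sit near one end. That can trip the ±2 limit even when the changes are well behaved. The rule then replaces a valid analysis of change in points with an analysis of change on a curved scale, where a one-point step counts more at one end than at the other. Three things are at stake:

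- the estimated size of the effect;
- whether it is declared significant;
- whether a reader can interpret it in units of the questionnaire.

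**Working it through.** **The plan's own figure.** For a paired design, n = ((z₀.₉₇₅ + z₀.₈₀)/d)² = ((1.960 + 0.842)/0.1)² ≈ 785, or 787 with the t distribution. At n = 850 the power for d = 0.1 is 83.0%, and the effect detectable with 80% power is 2.802/√850 = 0.096. The sample size statement is met, and nothing below disputes it.

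**Is the transformation needed to protect the test?** Scores were simulated on the stated 6–24 range with n = 850. The scores had skewness of about 3.2 and the differences about −0.3. The untransformed paired t-test had a type I error of 0.048 against a nominal 0.05. At this size, the transformation protects against nothing in the whole-group analysis.

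**Can the rule trigger when the differences are unremarkable?** The following is a constructed example, not trial data: mood on the 1–5 scale, 850 pairs.

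| Pre → post | Students | Raw change | Reflected log, −ln(6−x) | Reflected square root, −√(6−x) |
|---|---|---|---|---|
| 1 → 2 | 50 | +1 | +0.223 | +0.236 |
| 2 → 3 | 50 | +1 | +0.288 | +0.268 |
| 3 → 4 | 20 | +1 | +0.405 | +0.318 |
| 5 → 4 | 70 | −1 | −0.693 | −0.414 |
| 5 → 5 | 660 | 0 | 0 | 0 |

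Skewness is −2.28 at baseline and −2.09 at post-test, so the rule triggers at both time points. The differences have skewness 0.19 and excess kurtosis 1.44, inside ±2 on both counts.

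**What the choice of scale does to the result.**

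- Raw: (50 + 50 + 20 − 70)/850 = +0.059 points; t = 3.65, p = 0.00027, improvement. The bootstrap 95% interval is 0.028 to 0.091.
- Reflected square root: p = 0.57, no detectable change.
- Reflected log: (50×0.223 + 50×0.288 + 20×0.405 − 70×0.693)/850 = −0.017; t = −2.26, p = 0.024, in the direction of worsening.

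The mechanism is the weighting. On the reflected log scale a 5-to-4 step counts ln 2 / ln(5/4) = 0.693/0.223 = 3.1 times a 1-to-2 step, although both are one point on the instrument.

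**How often does the direction change?** Two simulations used assumed beta-shaped scores with pre–post correlation 0.2 to 0.8.

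- In data sets where the skewness rule triggered, the log changed the sign in 18 of 1,032 (1.7%) on the 6–24 scale and in 6 of 1,439 (0.4%) on the 1–5 scale. Both results were never significant.
- When only transformations that brought skewness inside ±2 at both time points were accepted (6–24 scale), 23 of 834 data sets (2.8%) changed sign. None was significant in both directions.

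**The case against.** The strongest reply is that the example does not follow the plan's own criterion. After the reflected log, baseline skewness is still about −2.1, so the transformation has not cured what triggered it and might not count as suitable. The reflected square root also leaves it at about −2.2. This stands: the example shows the mechanism, not a faithful run of the rule to a successful end.

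A reader might infer from it that the rule is liable to turn improvement into deterioration. The evidence does not support that. Other constructed sets with significant reversals, one on the 6–24 range among them, have differences that themselves fail ±2, so a check on the differences would have flagged them too. Significant reversals with log scores inside ±2 skewness at both times were found only in contrived data whose differences and log-scale kurtosis exceed ±2. In the less contrived simulations, sign changes were rare and never significant both ways.

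Four further replies have force:

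- The text neither names nor excludes the differences, so applying the screen to the pre and post scores is a reading, though the natural one. It is also not stated whether a five-category emoji item counts as continuous under this rule.
- A reader might say that the transformed test departs from a mean change fixed in the objectives. The Objectives state directions only and the Primary outcomes section gives percentage targets, so neither specifies a raw mean change.
- Which transformation is used, whether both time points receive the same one, and how results are back-transformed are details that an analysis plan not shown here may settle. Their absence is not counted as an error.
- The large-sample argument is for about 850 pairs. It does not automatically cover age and gender subgroups, whose sizes are not given.

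None of this removes the central point. The article states a positive rule, and the rule transforms on the basis of distributions that the chosen test does not depend on.

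**Conclusion.** The concern holds in a limited form, and the wording should be corrected. As naturally read, the rule screens and transforms the pre and post scores when only the paired differences, or their mean, matter. At about 850 pairs the untransformed test is sound without it. On bounded scores the rule can trigger when the differences are unremarkable; size and significance can then depend on the transformation chosen, and the result leaves the instrument's scale. The constructed example shows p moving from 0.00027 to 0.57 between two scales. It illustrates what is possible and does not forecast this trial's data.

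Reversal of direction is possible but rare: 0.4% to 2.8% of simulated data sets, under assumed score shapes and correlations. It is not the reason to change the plan.

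Confidence is high on the statistical principle and moderate on the practical effect. The latter depends on how skewed the scores turn out to be, which transformation is used, and the reading of continuous variables as the pre and post scores.

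**What to change.** Replace the transformation sentence with an assessment of the distribution of the paired differences. State that the untransformed within-student change is the primary analysis for all four outcomes. Where the differences are markedly non-normal, particularly in small age or gender subgroups, report a bootstrap confidence interval for the mean change or a signed-rank test as a sensitivity analysis.

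The cost is one sentence of analysis text and a little extra analysis. It needs no additional data and no change to the sample size.

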### Ethical considerations

Ethical approval was obtained from the Joint Chinese University of Hong Kong and New Territories East Cluster Clinical Research Ethics Committee prior to conducting the study (CREC Ref. No: 2022.659-T) registered on 23 March 2023. The study complies with the declaration of Helsinki with a statement of ethical principles for medical research involving humans. The ICH-GCP E6(R3) standards which is a harmonised standard that protects the rights, safety and welfare of human subjects and minimises their exposure to risk products [18]. Parental consents will be obtained through the School Communication System. Information sheet and parental consents will be distributed to parents through the school communication mails. Each participant’s questionnaire will be coded with a number. School and students’ names will not be released in the publications. Students can withdraw from the study anytime without any penalty in their routines and schooling. All the research data will be kept in a locked cabinet to protect the participant’s privacy.

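### The paired t-test discards the pre-tests of students without a post-test, so in this single-group study loss related to the pre-test level would bias the mean change

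*Protocol article*

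**What the plan says.** The Statistical analysis section of the protocol article gives a single inferential method for all four outcomes, overall and within age and gender subgroups: "Paired sample t-test will be used to compare the change of each outcome (mood, anxiety, social, playfulness) at post-test with respect to pre-test". The Methods section sets two measurement times, before and after the programme, with nothing in between.

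The Population section starts from the school rolls ("There will be 1,063 children and adolescents aged 6–18 years old"), takes at least 90% as eligible and willing, and adds that "the attrition rate would be less than 10" per cent. It concludes: "It is therefore expected to have at least 850 children completing the program and outcome assessments". That number "allows to detect a change in an outcome of effect size as small as 0.1 with 80% power". Ethical considerations adds: "Students can withdraw from the study anytime without any penalty in their routines and schooling".

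The plan therefore expects some loss, counts completers for its power, and analyses change with a method that can use completers only.

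**The concern.** A paired t-test works on within-student differences, and a student with no post-test has no difference. The resulting mean change estimates the change in all enrolled students only if loss is unrelated to both the pre-test level and the change.

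If students with better pre-test scores leave more often, those who stay start below the average of all enrolled students. They then regress towards that average by post-test, which reads as benefit. If students with worse scores leave, the same mechanism hides benefit.

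Two features of this study make that matter. With one group, no comparison arm suffers the same loss, so nothing cancels. And the study is sized for a standardised effect of only 0.1, so a bias that would be trivial against a large target is a visible share of this one. A sample of about 860 pairs shrinks the standard error but leaves the bias as it is.

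**Working it through.** **The plan's own figures**

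- Enrolled: 1,063 × 0.9 = 957. Completers at 10% loss: 1,063 × 0.9 × 0.9 = 861, which agrees with at least 850.
- Pairs needed for effect 0.1, 80% power, two-sided 0.05: ((1.960 + 0.842)/0.1)² = 785 (787 with the exact t).
- With 850 pairs, power at 0.1 is 83%. The power statement holds, and because 850 already counts completers, attrition costs no further power.

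**Bias when loss depends on the pre-test**

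Inputs from the documents: 957 enrolled, and attrition *a* with a ceiling of 10%. Assumptions, because the documents give no value: no true change, equal variances at both times, leavers *g* = 0.5 outcome SD better than completers at pre-test, and pre-post correlation *r* of 0.3, 0.5 or 0.7.

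- Completers start *a × g* below the mean of all enrolled students: 0.10 × 0.5 = 0.05 SD.
- Their apparent improvement is *a × g × (1 − r)* in outcome SD.
- The SD of change is √(2(1 − r)) outcome SD, so the bias in SD of change is *a × g × √((1 − r)/2)*. This is the natural scale for an effect size of 0.1 in a paired test.
- The rejection rate comes from the non-central t with non-centrality equal to bias × √n.

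| Attrition (pairs) | r | Bias, outcome SD | Bias, SD of change | Share of 0.1 | Rejection |
|---|---|---|---|---|---|
| 10% (861) | 0.3 | 0.035 | 0.030 | 30% | 14.0% |
| 10% (861) | 0.5 | 0.025 | 0.025 | 25% | 11.3% |
| 10% (861) | 0.7 | 0.015 | 0.019 | 19% | 8.8% |
| 5% (909) | 0.3 | 0.0175 | 0.015 | 15% | 7.3% |
| 5% (909) | 0.5 | 0.0125 | 0.0125 | 12.5% | 6.6% |
| 5% (909) | 0.7 | 0.0075 | 0.010 | 10% | 6.0% |

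Simulation (4,000 repetitions, 957 students, logistic dropout on the pre-test giving the same 0.5 SD gap) agrees. At 10% loss the paired test has bias 0.035, 0.025 and 0.015 outcome SD and rejects in 14%, 12% and 8% of studies. The likelihood estimate using all pre-tests has bias below 0.001 and rejects in about 5%. Slightly different settings of the gap move the paired test's rejection rate within about 8 to 15%.

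**Bias when loss depends on the change itself**

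Bias = *a* × (mean change in completers − mean change in leavers). With *a* = 0.10 and a gap of 0.25 or 0.50 SD of change, it is 0.025 or 0.050, and with 861 pairs rejection is 11.3% or 31%. A model using the pre-tests does not remove this part, because the quantity driving the loss is never observed.

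**Why filling in zero change would not help**

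Let *m* and *s* be the mean and SD of change in 861 completers. Adding 96 zeros gives a mean of 0.9*m*, an SD of about *s*√0.9 and a t statistic of 0.9*m*√957/(*s*√0.9) = *m*√(0.9 × 957)/*s* = *m*√861/*s*. That is the paired t statistic again. In simulation with leavers 0.5 SD worse in change, rejection is 30.4% with and without the zeros.

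A delta adjustment does move the result: if leavers changed by δ less than completers, the mean becomes *m* − 0.10δ. Completers need a mean of about 1.96/√861 = 0.067 SD for significance, and δ = 0.5 takes 0.05 off it.

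**The case against.** The strongest reply is that this is a missing-data question in disguise. The article neither states a rule for absent post-tests nor rules out imputation or sensitivity analysis, and such detail commonly sits in a full protocol or analysis plan that is not shown. That silence is indeed no finding. The article does, however, fix the estimator, and the one it names works on complete pairs. A method that uses data already collected can be compared with it on its merits.

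Three further replies stand and limit the point. The gap between leavers and completers is assumed and could be zero. Ten per cent is a ceiling, since the Population section says less than that, and at 5% loss the rejection rate is close to nominal. The Discussion already concedes that the uncontrolled design cannot rule out a placebo effect, beside which 0.02 to 0.03 SD is secondary.

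A reader might infer that the bias reaches half of the effect sought, 0.05 SD, with about 31% rejection. The documents do not support that as a statement about this study. It needs loss at the full ceiling together with leavers whose change differs by 0.5 SD, five times the effect sought. No passage gives any such figure, and the mixed model would not repair that case. Nor should a reader infer that the sample-size statement is wrong; it is not.

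**Conclusion.** The point holds in a limited, conditional form. The only stated analysis drops students without a post-test, and with no control arm, loss related to the pre-test level would bias the mean change. Its size rests on assumptions. With a gap of about 0.5 SD at pre-test and correlations of 0.3 to 0.7, the bias is about 0.02 to 0.03 SD of change at the 10% ceiling, with rejection of about 8 to 15% instead of 5%. It is about half that size at 5% attrition, and zero if loss is unrelated to both pre-test and change. The paired t-test is valid if the pairs are complete; the change is worth making because a better method is available at little cost. Confidence is medium, because nothing in the documents tells us how leavers differ.

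**What to change.** In the Statistical analysis section, replace the paired t-test with a repeated-measures linear mixed model for each outcome. Use time (pre, post) as the repeated factor, an unstructured within-student covariance, and age, gender and school as covariates. Fit it to every consented student with a pre-test. Without covariates and with complete data it reproduces the paired t-test, so nothing is lost if attrition proves negligible.

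Add one delta-adjusted sensitivity analysis for loss that depends on the unobserved change. Vary the leavers' assumed change over a stated range, for example from 0 to 0.5 SD worse than completers, and report whether each conclusion holds across it. Setting leavers' change to zero should not serve this purpose, because it leaves the t statistic unchanged.

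The cost is a few sentences and slightly more analysis work in the SPSS package already named, with no new data. The downside is that the sensitivity analysis may give a less favourable figure.

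### Four unranked primary outcomes are tested at 0.05 overall and again within age and gender subgroups, with no rule for what may be claimed and no test that could show a subgroup difference

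*Protocol article*

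**What the plan says.** The Objectives section gives four directional expectations: mood, anxiety, self-regulation with social skills, and playfulness. The Primary outcomes section attaches a separate target to each of the four and ranks none above the others. Its opening sentence is looser: it leaves out mood and lists negative emotions apart from anxiety. The count of four therefore rests on the numbered objectives and on Statistical analysis, which names mood, anxiety, social and playfulness.

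Statistical analysis prescribes a paired t-test of each outcome "at post-test with respect to pre-test within group and subgroups (age and gender") and performs all analyses "with level of significance set at 0.05". It names no comparison between subgroups and does not give the number of age bands.

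The Population section expects "at least 850 children completing the program and outcome assessments" and says this number "allows to detect a change in an outcome of effect size as small as 0.1". The power attached to that claim is 80%, for a two-sided test at 0.05. The statement concerns one outcome tested once.

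**The concern.** Two separate questions arise.

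The first is the error rate. Four primary outcomes, each with its own claim, give four chances of a false positive, and the subgroup repeats add more. Nothing in the text says whether one success is enough, whether all four are needed, or whether the subgroup results carry any claim. At stake is whether a report of benefit on at least one primary outcome has anything close to a 5% false-positive risk, and whether the power statement still applies once that risk is controlled.

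The second is what the subgroup tests can answer. A pre-post test inside girls and another inside boys asks twice whether change occurred. It does not ask whether the change differs. A significant result in one and a non-significant result in the other invites a conclusion that the method cannot support.

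**Working it through.** **Inputs.** From Population: 1,063 pupils, 90% eligible and willing, attrition below 10%, 850 completers, effect size 0.1, two-sided 0.05, 80% power. From Statistical analysis: four outcomes, paired t-test, 0.05. Assumed: the effect size is the mean change divided by the SD of change; there are two gender and two age groups of equal size; outcome correlations lie between 0 and 0.7; clustering by school is ignored.

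**The plan's own figure.**
- Completers: 1,063 × 0.9 × 0.9 = 861, consistent with at least 850.
- n for an effect of 0.1: ((1.960 + 0.842)/0.1)² = 785, or 787 with the exact t distribution.
- Power at n = 850: 0.1 × √850 = 2.915; Φ(2.915 − 1.960) = 83%.
- Effect detectable with 80% power: (1.960 + 0.842)/√850 = 0.096, which rounds to 0.1.

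The stated figure is sound for one outcome at 0.05.

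**Four primary tests, any one sufficient.**
- Independent: 1 − 0.95⁴ = 18.5%.
- Equally correlated test statistics, by simulation: 17.4% at 0.3, about 15.5% at 0.5, 13.1% at 0.7.

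**Adding the subgroup tests.** Four outcomes × (whole group + 2 genders + 2 age groups) = 20 tests. The whole-group test and the subgroup tests use the same children, so they are not independent. A simulation from four equal gender-by-age cells keeps that overlap. The chance of at least one false positive is about 52% with independent outcomes, 49% at correlation 0.3 and 45% at 0.5. It falls further at stronger correlation.

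**Power once the four outcomes are controlled.** The strictest Holm step is 0.05/4 = 0.0125 (z = 2.498).
- Power at n = 850: Φ(2.915 − 2.498) = 66%.
- Detectable effect: (2.498 + 0.842)/√850 = 0.115.
- n for 80% power at 0.0125: 1,119 completers (exact t), more than the 1,063 pupils in the six schools.
- Holm relaxes after each rejection. If all four true effects are 0.1, simulated average power per outcome is about 77% with independent outcomes and 74% at correlation 0.7.

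**Subgroup tests under an identical effect.** Take a true change of 0.1 SD in both of two halves of 425.
- Power of each: 0.1 × √425 = 2.062, giving 54%.
- One significant, the other not: 2 × 0.539 × 0.461 = 50%.

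**Direct test of a difference in change, 425 against 425.** The standard error is √(2/425) = 0.0686 SD of change.
- Power for a difference of 0.1: Φ(0.1/0.0686 − 1.960) = 31%.
- Difference detectable with 80% power: 2.802 × 0.0686 = 0.19.

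**The case against.** **Adjustment may be unnecessary.** The four objectives are separate hypotheses on separate scales, and judging each at 5% is a defensible position. The abstract also describes the evaluation as preliminary. This part stands: the inflation arises only if success on any one outcome may be claimed, and it would vanish if all four had to succeed. But the protocol states neither rule, and its abstract speaks of confirming the objectives.

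**Multiplicity could sit in an unseen analysis plan.** That would answer a silence. Here the article itself fixes 0.05 for all analyses and fixes the within-subgroup t-test as the subgroup method, so a stated choice is in question.

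**The primary targets are percentages (over 80%, over 70%), not p-values.** If those also had to be met, a false claim would be harder to reach. The protocol does not say how the targets and the t-tests combine, so this cannot be relied on.

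**No differential effect is promised.** Correct. None of the four objectives concerns age or gender. A reader might infer that the protocol plans to claim that the programme works better in one subgroup; the text does not support that. The point is only that the named method could not support such a claim if one were drawn from it.

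**The size is easily overstated.** A reader might compute 1 − 0.95²⁰ = 64% for the 20 tests. That treats nested tests on the same children as independent, which they cannot be. A reader might also take 66% as the power under Holm, when it is the power at its strictest step only.

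**Larger threats exist.** In a single-group pre-post study, maturation and regression to the mean are greater risks than multiplicity, and Holm does not reduce them. That limits the weight of this point without answering it.

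**Conclusion.** The point holds within limits. As written, the analysis allows a claim on any of four primary outcomes at 0.05, with a false-positive risk of about 13-17% at plausible correlations and at most 18.5%. That rests on an any-one-outcome reading, which the protocol neither states nor excludes. With subgroup tests included, the figure is about 45-52%, which rests on two gender and two age groups of equal size and outcome correlations of 0.5 to 0.

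The within-subgroup tests do not address whether the effect differs. Their pattern would disagree about half the time when it does not differ, given 0.1 SD in each of two halves of 425. This is a weakness of the chosen method, not a contradiction in the protocol.

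The sample size statement is not wrong. It holds for one outcome at 0.05 and does not carry over to four outcomes under family-wise control.

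**What to change.** 1. State the claim rule. If any single outcome may be claimed, apply Holm across the four primary outcomes at an overall two-sided 0.05.
2. Restate power at n = 850 for an effect of 0.1: 83% for a single test at 0.05, 66% at the strictest Holm step, and about 74-77% on average if all four effects are 0.1. Give the effect detectable at 0.0125 as 0.115. All of these are before any allowance for clustering by school.
3. Report the change in each age and gender subgroup with a confidence interval, labelled descriptive, without significance claims.
4. If differences by age or gender are of interest, examine them only by regressing the change score on gender and age. These coefficients are the interactions with time. Label the results exploratory.

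The cost is in wording and analysis; no new data or participants are needed to adopt it. The stated power becomes less favourable, and 80% power for 0.1 at the strictest step is out of reach in these six schools. The interaction test is weak, with about 31% power for a difference of 0.1 SD, so a non-significant interaction must not be read as evidence that the effect is the same.
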